## Abstract

**Background:**

Posterior spinal fusion (PSF) for the correction of idiopathic scoliosis is associated with severe postoperative pain. Erector spinae plane block (ESPB) has been proposed to provide analgesia and reduce opioid consumption. We aimed to investigate the effect of bilateral ultrasound-guided single-shot ESPB on postoperative analgesia in pediatric patients undergoing PSF.

**Methods:**

This double-blinded, randomized controlled trial will enroll 74 AIS patients undergoing elective PSF. Participants will be assigned to the ESPB group or control group at a 1:1 ratio. Patients in the ESPB group will receive ultrasound-guided bilateral ESPB preoperatively, and patients in the control group received sham ESPB using normal saline. The primary joint endpoints are the area under the curve (AUC) of numerical rating scale (NRS) score and opioid consumption in postoperative 24 h. The secondary endpoints are numerical rating scale (NRS) score and opioid consumption at postoperative 0.5, 3, 6, 9, 12, 24, 36, and 48 h, rescue analgesia, recovery outcomes, and adverse events.

**Discussion:**

At present, studies investigating the effect of ESPB on pediatric patients are still needed. This study focuses on the effect of ESPB on pediatric patients undergoing PSF on postoperative pain control and intends to provide a new strategy of multimodal analgesia management for major spine surgery.

**Trial registration:**

Chinese Clinical Trial Registry ChiCTR2300074505. Registered on August 8, 2023.

**Supplementary Information:**

The online version contains supplementary material available at 10.1186/s13063-024-08331-2.

## Introduction

Adolescent idiopathic scoliosis (AIS) is one of the most common type of scoliosis, with a global prevalence of 1–4% [1]. AIS can occur in children under 3 years of age but usually affects patients aged 10 years of age to maturity [2]. It is defined by a three-dimensional progressive deformity of the spine caused by a complex interplay of genetic, internal, and environmental factors [3]. Severe deformity affects the physical and mental health of young people [1] and curves greater than 40° require surgery [1]. To correct the deformity, standard posterior spinal fusion (PSF) is the surgical treatment for AIS patients [4]. Due to the invasiveness of the procedure, long-lasting reflex muscle spasms, and deep somatic pain caused by tissue trauma, PSF is associated with severe and excruciating postoperative pain [5]. Inadequate pain control is associated with poor outcomes, late mobilization, and hospital discharge [6]. Moreover, younger age is thought to be an independent factor of increased pain after surgery [7], and therefore in many pediatric patients, strong doses of opioids need to be administered for postoperatively pain control [8]. Thus, a multimodal analgesia approach combined with regional blockage is important to optimize pain control and minimize adverse effects from opioids after scoliosis surgery.

Erector spinae plane block (ESPB) is a newly developed regional anesthesia originally reported for thoracoabdominal analgesia. The local anesthetic (LA) is injected beneath the erector spinae muscle and superficial to the vertebral transverse process and is expected to block not only the ventral rami of spinal nerves [9] but also the dorsal rami innervating the back [10–12] and, depending on dermatomal level placement and volume injected, lead to a sensory blockade involving dermatomes from T1 to sacral dermatomes [9]. The most plausible mechanism of ESPB currently is the spreading of LA on nerves passing within or contiguous with the erector spinae muscle through [13].

In practice, the transverse process can be the ultrasonographic landmark, which makes ESPB easy to operate, and the endpoint for the needle is away from the pleura and neuraxial structures, leading to fewer risks to nearby tissue and structures than neuraxial techniques [14]. As an effective postoperative analgesia technique, ESPB has now been used in a broad range of surgical interventions [15–18] and provides a superior analgesic effect [19,20] and reduced opioid consumption during the first 24 h operatively compared with systemic analgesia [21,22]. However, ESPB is placed mostly in adult patients (90.5%) [23]. Apart from case reports [24] and retrospective studies [25], its utility in pediatric patients remains unclear [26].

Therefore, we aimed to evaluate preoperative ultrasound-guided single-shot ESPB versus a control group (no block) in AIS patients undergoing PSF regarding postoperative pain score and dosage of opioid used.

## Material and methods

### Objective

The primary hypothesis is that ESPB reduces pain score and opioid consumption within 24 h postoperatively for AIS patients after PSF surgery compared with patients who received no block.

### Study design

This single-center, double-blinded, exploratory randomized controlled trial was approved by the Clinical Research Ethics Committee of Beijing Children’s Hospital ([2023]-E-064-Y), and its design has been completed in strict accordance with the SPIRIT 2013 statement. This study was prospectively registered before patient enrollment at https://www.chictr.org.cn (registration number: ChiCTR2300074505, principal investigator: [name]) on August 8, 2023. Written informed consent will be obtained by a research assistant from the participants or their legal guardians in the case of children under 16 prior to study commencement. The findings will be disseminated through peer-reviewed publication, conference presentation, and social media to increase topic area knowledge and inform future research among researchers and healthcare professionals. This protocol adheres to the applicable Consolidated Standards of Reporting Trials (CONSORT) guidelines. The flowchart diagram of the study is presented in Fig. 1, and the SPIRIT figure of enrollment, interventions, and assessments is illustrated in Table 1.

**Fig. 1 Fig1:**
[figure not shown]
Flowchart of the study design. Abbreviations: ASA, American Society of Anesthesiologists; BMI, body mass index; ESPB, erector spinae block; PCIA, parent-controlled intravenous analgesia; PSF, posterior spinal fusion

**Table 1 Tab1:** Trial schedule of enrollment, interventions, and assessments

**Time point**	**Study period**											
	**Enrollment**	**Allocation**	**Post-allocation**									**Close-out**
	− 1 D	0	PRE	POS 0.5 h	POS 3 h	POS 6 h	POS 9 h	POS 12 h	POS 24 h	POS 36 h	POS 48 h	Discharged day
**Enrollment**												
Eligibility screen	X											
Informed consent	X											
Allocation		X										
**Interventions**												
ESPB			X									
No block			X									
**Assessments**												
PCA boluses					X	X	X	X	X	X	X	
NRS score				X	X	X	X	X	X	X	X	
Postoperative complication				X	X	X	X	X	X	X	X	X
Mobilization				X	X	X	X	X	X	X	X	X
Gastrointestinal function				X	X	X	X	X	X	X	X	X
QoR-15 score								X		X	X	
Length of stay												X
Total cost												X

*PRE* preoperative, *POS* postoperative, *ESPB* erector spinae plane block, *NRS* numeric rating scale, *QoR-15 score* quality of recovery-15

### Participants

We include patients aged less than 18 years undergoing elective PIS with an American Society of Anesthesiologists (ASA) physical status of I to II. The exclusion criteria are as follows:Severe comorbidities such as cardiac insufficiency and liver or renal dysfunction;contraindications of ESPB: coagulation abnormality, hemorrhagic diseases, puncture site infection, and preexisting neurological deficits;Allergy to LA or other study medication;Chronic pain characterized by preoperative opioid use for more than 3 months;Cognitive impairment or mental illness rendering the patient unable to cooperate in the pain assessment; andInability of the guardian to use a postoperative analgesia pump.

### Recruitment

The participants will be enrolled at our institution, which is a national scoliosis diagnosis and treatment center serving more than 200 children with scoliosis each year. Therefore, we used a large patient population as the basis of this trial. In addition, the following methods and strategies were used to ensure that sufficient participants were recruited: determining the type of subjects who were suitable and ensuring that the recruitment criteria were clear and specific; establishing partnerships with local healthcare providers, community organizations, and physicians to promote the trial and attract suitable patients to participate; posting information about the trial through medical journals, hospital websites, media, forums, the internet, and other channels to seek participants; and strictly complying with the rules of the ethics committee and laws and regulations to ensure the safety and rights of participants during the recruitment process.

### Randomization and blinding

Patients will be screened the day before surgery by the investigator. After assignments, the patients will be randomized on the morning of the day of surgery to the ESPB group or the control group at a 1:1 ratio according to a computer-generated sequence of random numbers generated by a third-party statistician not otherwise involved in the trial. Consecutively numbered, opaque, sealed envelopes will be used to conceal the sequence. Nurse anesthetists who will not participate in the follow-up visit will assign participants to the two groups. The LA given to patients in the ESPB group and the normal saline with the same volume given to patients in the control group will also be prepared by the anesthesia nurse according to the group allocation. The attending anesthesiologists who will implement the treatment, the patients and their guardians, and the investigator responsible for follow-up will be blinded to the randomization groups. The statistician will be unblinded to the allocation only after all the data have been collected, entered into the database, and cleaned, and the primary analysis has been completed. Emergency blinding is performed in the case of serious adverse events or patients needing urgent resuscitation so that the physician knows the patient grouping for resuscitation and reports it to the Principal Investigator.

### Intervention

#### General anesthesia and intraoperative pain management

All patients will undergo standardized monitoring. General anesthesia is induced with intravenous sufentanil 0.5 μg/kg, propofol 2.0 to 3.0 mg/kg, and cisatracurium 0.1 mg/kg, followed by propofol 0.1 to 0.2 mg kg^−1^ min^−1^ and sevoflurane 1–1.5 MAC for anesthesia maintenance to keep a bispectral index between 40 and 60. Remifentanil can be infused at 0.1 to 0.2 μg kg^−1^ min^−1^ if necessary. The anesthetic, vasopressors, fluid volume, and infusion speed are adjusted to maintain the hemodynamic parameters within 20% of the preoperative baseline values. After intubation, patients in the ESPB group will receive a bilateral ultrasound-guided erector spinae plane block using ropivacaine, and patients in the control group will receive a bilateral sham block and be turned to the prone position to begin the surgery. The intraoperative analgesic protocol consisted of intravenous administration of 5 mg dexamethasone before general anesthesia induction and 1 mg/kg dexmedetomidine 20 min before the end of surgery. Ibuprofen at 10 mg/kg (maximum: 400 mg) was diluted to a concentration less than 4 mg/ml using saline and administered intravenously at the beginning of surgery and thereafter every 6 h at the ward until 48 h postoperatively.

##### Surgical procedure

The surgeon will make a posterior midline incision and expose the spine gradually. After inserting the screws, rods are placed into the screws to correct the deformity. Local bone grafts are placed around the osteotomy sites. After incision suturing, the patients will be weaned from mechanical ventilation and extubated. All patients will be admitted to the post anesthesia care unit (PACU) and then discharged to the ward with a full evaluation of conscious state and vital signs.

##### Erector spinae plane block

For patients who undergo posterior spinal fusion that spans ≤ 5 vertebral segments, bilateral ESPB will be performed at the midpoint of the incision [25]. For patients with anticipated fusion of ≥ 6 segments, the planned incision will be divided into two segments, and bilateral ESPB will be performed at the midpoint of each segment.

A high-frequency (4 to 15 MHz) linear transducer (Labat SP; Wisonic, Shenzhen, China) will be used to identify the erector spinae muscle and transverse process at 2–3 cm lateral to the spinous process. After aseptic conditions, a 21-gauge block needle (5 cm, Hakko disposable monopolar nerve blockage needle, Hakko Co., Ltd., Nagano, Japan) will be inserted using the in-plane approach to access the transverse process. Once the correct location is confirmed, 0.3% ropivacaine in a volume of 0.5 ml/kg per side per level (maximum of 3 mg/kg) will be injected into the musculofascial plane between the erector spinae muscle and transverse process. The procedure is then repeated on the other side.

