### Safety considerations

The researchers will adhere to the operation protocol strictly to minimize the risk of adverse events (AEs) and severe adverse events (SAEs). Medications are prepared and double-checked by specialized nurses. The operation of ESPB will be conducted by a fixed and experienced team under the extensive monitoring of vital signs to avoid AEs such as local anesthetic systemic toxicity. Experts are ready to provide immediate support if needed. For participants who are harmed during the investigation, the cost of treatment will be borne, and financial compensation will be paid in accordance with the relevant national regulations and laws.

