## Discussion

Typically, as the standard procedure for surgical management of AIS, PSF involves three to eight levels of spinal exposure, massive blood loss, and extensive muscle dissection, which causes severe postoperative pain,^28^ thus requiring high opiate usage [29,30]. In addition, because of the effect of sevoflurane on intraoperative neurophysiological monitoring (IONM) of movement, the large use of intraoperative opioids, usually remifentanil, seems to be necessary but may be associated with hyperalgesia in the postoperative period, further leading to a postoperative increase in opioids [31], and an increased risk of complications [32]. Physicians have taken an effort to decrease opioid prescriptions by using multimodal analgesia approaches, including neuraxial or regional techniques, in the postoperative period [33]. ESPB has earned its efficacy and reliability in adult patients undergoing lumbar spine surgeries [34], cervical spine surgeries [35], and lumbosacral spine [11,36] and thoracic spine surgeries [10]. Recent studies have even reported that ESPB shows more reliable spread and cover to the dorsal rami than to the ventral rami [37]. If it can be used for scoliosis surgery, there will be several advantages: it has no effect on IONM, provides stable hemodynamics, reduces blood loss, and, most importantly, reduces the pain and the use of opioids.

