ESPB are feasible following our protocol. A single injection can block spinal nerves at multiple levels because of the extensive spread of LA in the musculofascial plane [9]. The dermatomal distribution of sensory loss by a single injection can cover the area from the parasternal to the midline of the lower back [38]. Because the number of segments invaded by idiopathic scoliosis is often greater and the lower thoracic segment ESPB may only spread to the L2–L3 level [37], we adhere to the following rule when choosing the plane of injection of ESPB: the midpoint of the involved segments (planned incision) is chosen in cases involving ≤ 5 segments. For example, for children undergoing fusion of L1−5 segments, we choose to make the injection at the L3 level, where the ESPB using 0.3% ropivacaine 0.5 ml/kg can subsequently diffuse to the L1−L5 levels to meet the surgical needs [39]. If fusion is planned for ≥ 6 segments, the incision is divided into two segments, and the midpoint of each segment is chosen as the injection site [24]. However, there are no pharmacokinetic data or solid conclusions on the maximal safe concentration and volume for ESPB so far [40]. The literature regarding pediatric use is even more limited. The volumes used in both our institution and previous publications are 0.3–0.5 mL/kg per side, with LA concentrations of 0.2% to 0.25% for infants and children, and 0.5% for adolescents [25]. However, it is imperative to emphasize that, to date, no pharmacokinetic data for ESPBs are available. This further reinforces the need to evaluate the safe maximal doses of concentration and volume for the age range [41].

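### The 3 mg/kg ropivacaine maximum has no stated scope, and the two-level block as written comes to a nominal 6 mg/kg

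*Protocol article*

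**What the plan says.** The dose is given in the Protocol article, section Erector spinae plane block: "0.3% ropivacaine in a volume of 0.5 ml/kg per side per level (maximum of 3 mg/kg"). The same section sets the number of injections. Fusions of up to five segments get one bilateral block. For six or more, "the planned incision will be divided into two segments, and bilateral ESPB will be performed at the midpoint of each segment".

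The Discussion returns to the regimen in four places:
- It gives an example of a fusion from L1 to L5 injected at L3, where "ESPB using 0.3% ropivacaine 0.5 ml/kg can subsequently diffuse" over the fused levels. This is a one-level case.
- It repeats the two-site rule ("the midpoint of each segment is chosen as the injection site") with no volume, maximum or adjustment.
- It reports local and published practice: "The volumes used in both our institution and previous publications are 0.3–0.5 mL/kg per side", at concentrations of 0.2% to 0.25% in infants and children and 0.5% in adolescents.
- It states that "there are no pharmacokinetic data or solid conclusions on the maximal safe concentration and volume for ESPB so far".

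On the extent of surgery, the Discussion says that "PSF involves three to eight levels of spinal exposure".

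**The concern.** The sentence sets a volume rule per side and per level, and then a maximum per kilogram without saying what the maximum covers. The two agree for a one-level block. For a two-level block they agree only if the maximum is not a per-patient limit.

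At stake is the ropivacaine dose in patients under 18, for a block whose safe maximum the article itself calls unsettled. Two-level blocks are a planned case: six to eight levels lie within the range that the article describes as typical. The nurse who draws up the syringes needs one target dose, and the same volume has to be prepared as saline for the control arm. The dose is also the intervention under test, so a two-fold ambiguity makes the trial harder to reproduce and interpret.

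**Working it through.** **Inputs**, all from the section Erector spinae plane block: concentration 0.3% = 3 mg/ml; volume 0.5 ml/kg per side per level; two sides; one level for fusions of five segments or fewer, two levels for six or more; maximum 3 mg/kg.

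**Formula.** Dose (mg/kg) = concentration × volume per injection × sides × levels.

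**One level, reproducing the stated figure.**
- Per injection: 3 × 0.5 = 1.5 mg/kg.
- Total: 1.5 × 2 sides × 1 level = 3.0 mg/kg, exactly the stated maximum.

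**Two levels.**
- Total: 1.5 × 2 sides × 2 levels = 6.0 mg/kg nominal, and 6.0 / 3.0 = 2.

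**What the maximum does to a two-level block under each reading:**

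| Maximum applies to | Nominal dose in that unit | Does it reduce the dose? | Total per patient |
|---|---|---|---|
| Patient | 6.0 mg/kg | Yes, by half | 3.0 mg/kg |
| Level (both sides) | 3.0 mg/kg | No | 6.0 mg/kg |
| Side (both levels) | 3.0 mg/kg | No | 6.0 mg/kg |
| Injection | 1.5 mg/kg | No | 6.0 mg/kg |

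Dose and maximum are both per kilogram, so weight cancels. The maximum binds in every two-level patient or in none. As an illustration at an assumed 40 kg, the nominal two-level block is 40 × 0.5 × 4 = 80 ml, or 240 mg, against 40 × 3 = 120 mg under a per-patient maximum.

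**Two ways to meet a per-patient 3 mg/kg with four injections:**
- Keep 0.3% and cut the volume: 3.0 / (3 × 4) = 0.25 ml/kg per injection. That is 0.25 × 2 = 0.5 ml/kg per side and 1.0 ml/kg in all.
- Keep 0.5 ml/kg and dilute: 3.0 / (0.5 × 4) = 1.5 mg/ml = 0.15%. That is 0.5 × 2 = 1.0 ml/kg per side and 2.0 ml/kg in all.

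So even once the scope is settled, the volume to draw up differs two-fold between compliant solutions.

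**The case against.** The strongest reply is that nothing stated is wrong. A weight-based volume with a maximum is a normal way to prescribe, and a maximum exists to override the nominal dose. A limit in mg/kg refers naturally to the patient. The other drugs in the article (ibuprofen, dezocine, acetaminophen) also carry maxima without naming the patient. On this view only preparation detail is left, which a condensed article may leave to the full protocol that it says is available on request. Specialized nurses double-check the medication, a fixed team performs the block, and there is "extensive monitoring of vital signs to avoid AEs such as local anesthetic systemic toxicity".

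Much of this stands. Per patient is the likeliest reading: it is the only one that gives the maximum any effect, and with 0.3% kept it yields 0.5 ml/kg per side, inside the range in the Discussion. The safeguards are real.

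Two things do not follow. First, the other maxima are absolute amounts (400 mg, 5 mg, 2 g per 24 h) that bind only in heavier patients. This one, read per patient, overrides the stated regimen in every two-level block, which is the only case where the words on level matter. The text therefore conflicts with itself in a planned group; it is not merely brief. Second, double-checking and monitoring do not define which dose is the correct one to prepare.

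A reader might infer that the trial gives children 6 mg/kg, or twice a safe dose. The documents do not support that. They do not show that 6 mg/kg was intended or given, and 3 mg/kg is the article's own limit, not an established toxicity threshold.

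**Conclusion.** The point holds in conditional form. The written two-level regimen totals a nominal 6 mg/kg. That is twice the stated maximum if the maximum is per patient, as is likeliest; under the other three readings it is permitted and the maximum is idle. One-level patients receive 3 mg/kg and comply on every reading.

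This rests only on the article's own concentration, volume and injection counts. How many patients are affected is unknown: the article gives a typical range of levels but no distribution. The full protocol may settle the scope, but nothing in the article does. Saline volume is matched to active volume (Randomization and blinding), so blinding is not threatened, and no sample size, significance level or analysis changes. It should be fixed because it concerns a pediatric dose limit and the remedy is short.

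**What to change.** In the section Erector spinae plane block, state that 3 mg/kg is the total ropivacaine dose per patient across all injections, and state the two-level regimen that meets it. Two options comply, and the choice is the investigators':
- **0.25 ml/kg of 0.3% per side per level.** This keeps 0.5 ml/kg per side in total, within the per-side range in the Discussion. Each site gets half the volume of a one-level block, and 0.25 would fall below 0.3 ml/kg if that range were meant per injection.
- **0.15% at 0.5 ml/kg per side per level.** This keeps the volume per site. The concentration is below all those listed in the Discussion, and the volume per side becomes 1.0 ml/kg, above the listed range as written.

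Use the same saline volume in the sham arm.

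The cost is a short wording change, with no extra patients and no change to the analysis. The clinical price is less volume or a weaker solution per level in two-level patients. Recruitment was under way when the article was written (Trial status). If two-level patients have so far received a different dose, the change should be a dated protocol modification, notified as Oversight and monitoring requires.
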